### Sample size and statistical power

The primary hypothesis of this study is that HF patients receiving the PCDM intervention will have improved health status over a 12-month follow-up period compared with those receiving usual care. The minimal clinically meaningful difference in KCCQ summary scores is 5 points, [18] and the standard deviation of change in KCCQ scores was estimated to be between 15 and 20 based on previous work [17,18]. Using a type I error rate (α) of 0.05, and an attrition rate of 30%, we originally estimated enrollment of 600 patients would have >80% power to detect a difference in KCCQ scores of ≥ 5 points assuming a standard deviation of 18. The data to date showed less than 20% attrition and a KCCQ standard deviation of 15 points. With the final enrollment of 392 patients, we will have over 80% power to detect a 5 point difference in KCCQ score.

### Analyses

All primary and secondary analyses will be conducted using an intention-to-treat approach. Patients will be analyzed in the arm to which they were randomized irrespective of treatment adherence. The baseline characteristics of patients will be summarized by study group and examined for differences. To examine the primary outcome, change in HF-specific health status as measured by the KCCQ, a likelihood-based random effects model using all available data will be implemented [24]. We will examine the magnitude and patterns of missing data to check the sensitivity of the model assumptions. Model parameters will be estimated using the SAS procedure MIXED (SAS Institute, Cary, NC). Most of the secondary study outcomes are continuous and will be analyzed using a similar mixed modeling approach. Rates of all-cause hospitalization and mortality and the proportion of patients in each study arm receiving guideline-concordant care at 12-months will be compared between study arms using a Chi-Square test. To examine medication adherence, the PDC for each study group will be compared as a continuous measure (t-test) and as the proportion of patients achieving a PDC > 0.80 (Chi-Square), a cut-off used in multiple medication adherence studies [25].

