## Background

Despite advances in chronic heart failure (HF) therapies, HF is a leading cause of disability, hospitalization, and death in the United States [1]. Moreover, HF has a major impact on patients’ health status, including their symptom burden (e.g. dyspnea), functional status, and health-related quality of life. However, few HF interventions have specifically targeted these critical patient-centered outcomes. In addition, diminished patient health status is predictive of HF hospitalization, mortality, and resource utilizations, yet health status has not been used to screen for patients to target disease management interventions [2].

While disease management has been variously defined and implemented, some previous studies have reported that HF disease management can reduce rates of hospitalization, and a few have demonstrated reductions in mortality, reductions in cost, or improvements in quality of life. However, many of these studies have been small, single-center trials of short duration, and the association between disease management and improved outcomes has been inconsistent [3-6]. Many HF disease-management studies to date have relied solely on nurse case management rather than multidisciplinary collaborative care, have not leveraged health information technology, and/or have had a limited focus on patient self-care. Most have not included screening and treatment of comorbid depression, or specifically targeted improvement in patient health status as the primary outcome [7]. The Patient-Centered Disease Management (PCDM) trial was designed to address these limitations.

The PCDM trial is evaluating the effectiveness of a collaborative care intervention with telemonitoring and evidence-based HF and depression management in an at-risk population of HF patients with diminished health status. All HF patients from participating centers were identified using existing VA electronic health record databases. The primary outcome of the PCDM trial is 1-year change in patient-reported HF health status, measured using the Kansas City Cardiomyopathy Questionnaire (KCCQ), comparing patients randomized to usual care versus the PCDM intervention. Secondary outcomes include depression, adherence to guideline-based therapies, hospitalizations, and mortality.

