## Methods/design

### Study design overview

The primary objective of the PCDM trial is to determine whether a collaborative care HF disease management intervention, including depression assessment and treatment, improves patient-reported health status between baseline and 12 months, as measured by the KCCQ. The study was funded by the United State Department of Veterans Affairs (VA) and conducted in four VA medical centers across the U.S. The VA’s comprehensive electronic medical record was used to identify potential participants for the study. All patients with HF at the four sites were screened with the KCCQ. Eligible patients with diminished heart failure-specific health status (KCCQ summary score <60) were invited to an enrollment visit. Patients provided informed consent, were randomized to the PCDM intervention or usual care, and were followed for a 12-month period. The study was approved by the Institutional Review Boards at each of the study sites.

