**Figure 1 F1:**
[figure not shown]
Patient-centered disease management (PCDM) for heart failure trial study population flow.

The study was purposefully designed to target patients with a diagnosis of HF in the VA electronic health record, irrespective of type of heart failure (e.g. with or without preserved left ventricular systolic function). Accordingly, the diagnosis of HF was defined as meeting any one of the following five criteria: (1) A primary inpatient hospital discharge diagnosis of HF (ICD-9 code 428.XX); (2) ≥2 secondary inpatient hospital discharge diagnoses of HF (ICD-9 codes 428.XX) and a primary inpatient hospital discharge diagnosis related to heart disease (ICD-9 codes 410.XX, 412.XX, 413.XX, 414.XX); (3) ≥3 secondary inpatient hospital discharge diagnosis codes related to HF; (4) ≥2 outpatient visit diagnoses of HF, excluding emergency department visits; (5) ≥2 secondary inpatient hospital discharge diagnoses of HF and ≥ 1 outpatient HF diagnosis. This case-finding methodology has been previously described [12]. The primary care provider of each patient was contacted by mail to inform them of the PCDM trial and to allow them to withdraw their patient from further consideration if they deemed the patient to be a poor candidate for study participation.

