### Randomization

At the enrollment visit, patients provided informed consent, completed baseline survey measures, and were then randomized. The random allocation sequence was computer generated (SAS version 9.1 procedure PLAN) using a uniform fixed randomization design with an allocation ratio of 1:1 and stratification by site.

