**Primary Outcome**					
HF-specific Health Status	KCCQ^*^	X	X	X	X

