**Secondary Outcomes**					
Depression	PHQ-9^†^	X	X	X	X
	SCL-20^‡^	X			X
Medication Adherence	PDC^§^	X	X	X	X
Guideline-Based Care	Criteria mapping	X			X
Hospitalizations, mortality	Medical Record Review, Self- or Surrogate Report				X

^*^ Kansas City Cardiomyopathy questionnaire.

† Patient health questionnaire-9.

^‡^ Hopkins symptom checklist-20.

^§^ Proportion of days covered.

The primary outcome, HF-specific health status, was measured using the KCCQ. The KCCQ is valid, reliable, sensitive to clinical change, and predicts hospitalization and mortality [2,17,18]. For the secondary outcomes, depression was measured using the PHQ-9 and the Hopkins Symptom Checklist-20 (SCL-20). The PHQ-9 is a valid and reliable instrument that provides a continuous measure of depressive symptoms [19]. The Hopkins Symptom Checklist-20 (SCL-20) is also a valid and reliable measure of depression symptoms [20]. To examine medication adherence, the proportion of days covered (PDC) will be calculated for each patient using established methods, based on the total number of days supplied for filled prescriptions over the observation time interval [21]. Primary medications to be evaluated will be angiotensin converting enzyme inhibitors, angiotensin II receptor blockers, beta-blockers, aldosterone antagonists, statins, digoxin, diuretics, and antidepressants. For a given patient, the proportion of guideline-concordant care will be determined using criteria mapping [15,22]. The guideline-concordant care analysis will be restricted to those patients who have a guideline indication for a medication class, such as beta-blockers for HF with left ventricular systolic dysfunction. Hospitalizations and mortality will be assessed through VA databases, supplemented by patient self-report. Vital status will also be ascertained via the VA Vital Status File which has a sensitivity of 98.3% and specificity of 99.8% compared to the National Death Index [23].

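### All-cause hospitalization is compared by an unadjusted chi-square although the article says the KCCQ predicts it: a valid test, but a small avoidable loss of precision on a secondary outcome

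*Protocol article*

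**What the plan says.** All references are to the protocol article.

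- **Analyses.** The method is named. One sentence opens with "Rates of all-cause hospitalization and mortality and the proportion of patients in each study arm", and the only test it gives for these outcomes is a chi-square. No covariate or site term is mentioned. The mixed model in the same section serves the primary outcome and the continuous secondary outcomes, not this one.
- **Outcome measures.** "The KCCQ is valid, reliable, sensitive to clinical change, and predicts hospitalization and mortality".
- **Background.** "diminished patient health status is predictive of HF hospitalization, mortality, and resource utilizations".
- **Randomization and Table 1.** Baseline questionnaires are completed before allocation, and KCCQ is one of the baseline measures. Allocation uses "an allocation ratio of 1:1 and stratification by site".
- **Study design overview.** "Eligible patients with diminished heart failure-specific health status (KCCQ summary score <60) were invited to an enrollment visit".
- **Setting and population.** VA inpatient discharge codes are used for case finding, beginning with "A primary inpatient hospital discharge diagnosis of HF (ICD-9 code 428.XX". Four of the five criteria use inpatient codes; the fourth is met by outpatient visits alone.

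**The concern.** The article names a predictor of hospitalization, measures it in everyone before allocation, and then fixes a test of hospitalization that cannot use it. This is more than a detail left to an analysis plan, because the test is stated.

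Adjusting for a prognostic baseline variable usually narrows the interval for the treatment effect in a randomized trial. Enrolment is final at 392, so further precision on this outcome has to come from the analysis. The article also plans to examine baseline differences between arms but names no adjusted analysis of hospitalization. Any adjustment introduced after an imbalance has been seen would be post hoc.

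**Working it through.** **1. The plan's own power figure.** No power is stated for hospitalization. The KCCQ figures reproduce with a two-sided α of 0.05 (sidedness assumed):
- Original plan: 600 × 0.70 / 2 = 210 per arm. SE = 18 × √(2/210) = 1.757, and Φ(5/1.757 − 1.96) = 81.2%.
- Final plan: 392 × 0.80 / 2 = 156.8 per arm. SE = 15 × √(2/156.8) = 1.694, and Φ(5/1.694 − 1.96) = 83.9%.

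Both agree with the stated power of over 80%.

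**2. Assumptions for hospitalization.** The documents do not give these:
- 392 patients analysed, 196 per arm, and a 40% control risk;
- KCCQ normal with mean 60 and SD 22, cut at 60 (SD within the cut about 12.7);
- odds ratio per 5 KCCQ points of 1.05 to 1.15;
- prior admission in 40% of patients, with odds ratio 1.0 (no information) to 3.0.

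The hard cut is a simplification. The limit applies to the mailed questionnaire, and baseline KCCQ is collected at the enrolment visit.

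**3. Precision.** R² = Var(individual risk) / [p(1 − p)]; SE ratio = √(1 − R²); effective N = 392 / (1 − R²). At p = 0.40:

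| OR per 5 KCCQ points | OR prior admission | R² | SE ratio | Effective N |
|---|---|---|---|---|
| 1.05 | 1.0 | 0.0037 | 0.998 | 393 |
| 1.10 | 1.0 | 0.0142 | 0.993 | 398 |
| 1.15 | 1.0 | 0.0301 | 0.985 | 404 |
| 1.05 | 1.5 | 0.0131 | 0.993 | 397 |
| 1.10 | 2.0 | 0.0405 | 0.980 | 409 |
| 1.15 | 3.0 | 0.0910 | 0.953 | 431 |

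KCCQ alone is worth about 1 to 12 extra patients (393 − 392 to 404 − 392). With a strong prior-admission effect the figure reaches 39 (431 − 392).

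**4. Power for hospitalization.** Treatment odds ratio 0.56, 4,000 simulated trials per scenario, chi-square against a logistic likelihood-ratio test adjusted for KCCQ and prior admission:
- weak prognosis (1.05, 1.5): 76.3% to 77.0%;
- middle (1.10, 2.0): 74.1% to 75.8%;
- strong (1.15, 3.0): 70.2% to 73.8%.

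The gain is 0.7 to 3.6 points. With no treatment effect the chi-square rejects in 4.4% to 5.0% of trials and the adjusted test in 4.8% to 5.6%, so a small part of the gain is a slightly more liberal test.

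With site terms included, KCCQ and site add about 1 to 2 points, KCCQ, site and prior admission add about 1 to 4, and type I error stays near 5%. A repeat of that model on the step 2 assumptions (four equal sites, 4,000 trials per scenario), testing the standardized risk difference, gave 0.4 to 1.7 and 1.3 to 4.2 points. The Monte Carlo SE of one power estimate near 75% is √(0.75 × 0.25 / 4,000) = 0.7 points, so the lowest gains cannot be told from nothing.

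**5. Mortality.** Assume 10% deaths, about 39 of 392. A model with arm, KCCQ and three site terms has 5 parameters, about 8 deaths each; at 5% deaths it would be about 4. Under a treatment odds ratio of 0.5 the likelihood-ratio test moves power from 41.2% to 41.9% and, at most, from 42.9% to 44.2%. Its type I error is 5.2% to 5.9%, against 4.8% to 5.2% for the chi-square. With site terms, the Wald test gained nothing: 0.44 for the chi-square against 0.42 adjusted, and 0.50 against 0.48.

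**The case against.** The strongest reply is that nothing here is an error. A chi-square comparison of randomized arms under intention to treat is valid. Saying that the KCCQ is prognostic does not contradict an unadjusted test of a secondary outcome, and an analysis plan not shown may add covariates. This stands as far as it goes: the point concerns efficiency, and it rests on the article naming a test that cannot use the predictor it endorses.

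A reader might infer more than the documents support:
- **That the chi-square is biased or misleading under baseline imbalance.** Chance imbalance is already allowed for in its error rate, which stays near 5% in the simulations.
- **That the gain is large.** With baseline factors discriminating at AUC 0.75, simulated power rises from 69.9% to 76.8%. No AUC is given, and the prediction is cited for the KCCQ or health status generally, not among patients selected for scores below 60. The Background statement also concerns HF admissions, whereas the outcome is all-cause.
- **That prior admissions are a known predictor already in hand.** The documents never call them prognostic. The case-finding text gives no look-back window and does not show that a count of admissions in the year before randomization was extracted.
- **That the shortfall from 600 to 392 makes this pressing.** The sample size was set on the KCCQ alone, for which 392 still gives over 80% power.
- **That mortality needs the same change.** Step 5 of the working shows no meaningful gain.

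**Conclusion.** The point holds for hospitalization only, as a minor efficiency improvement. The stated test is valid but sets aside a baseline value that is already collected and that the article describes as predictive. The loss is about 1 to 4 points of power: the upper part requires an informative prior-admission variable, and KCCQ with site alone gives about 1 to 2. If the KCCQ is weakly prognostic within the enrolled range, the loss is close to nil. These sizes depend on an assumed 40% control risk, an assumed treatment effect and assumed prognostic odds ratios. The direction needs only that baseline KCCQ carries some information about admission. The primary outcome is unaffected, and the case for adjusting mortality does not hold.

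**What to change.** In the Analyses section, before outcomes are compared by arm:
- State the 12-month all-cause hospitalization analysis as a logistic regression on arm, baseline KCCQ (continuous) and site. Add prior VA admission, with its look-back period defined in advance, if it can be drawn from the same VA records.
- Report the standardized risk difference, meaning the difference between average predicted risks with all patients assigned to each arm in turn, with its 95% CI. This keeps the comparison on the scale of the two proportions in the chi-square.
- Keep the chi-square as the supportive unadjusted result.
- Leave mortality with the unadjusted comparison.

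The cost is a short change of wording, slightly more analysis work and reliance on a working model for the covariates. No new patients or questionnaires are needed. The prior-admission variable may need a further extraction from VA records, and the change is still worth making without it.

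### Guideline-concordant care is defined as a proportion within each patient but compared as a proportion of patients by an unadjusted chi-square test, which leaves the baseline value and the site strata unused

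*Protocol article*

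**What the plan says.** The protocol article describes this endpoint in two places.

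- **Outcome measures, text below Table 1.** The quantity belongs to the patient: "For a given patient, the proportion of guideline-concordant care will be determined using criteria mapping". The analysis set is then narrowed: "The guideline-concordant care analysis will be restricted to those patients who have a guideline indication for a medication class", with beta-blockers in systolic dysfunction as the example. In Table 1 the row "Guideline-Based Care" is marked at baseline and at 12 months.
- **Analyses.** The comparison is between groups of patients: "the proportion of patients in each study arm receiving guideline-concordant care at 12-months will be compared between study arms using a Chi-Square test". This sentence gives no rule for counting a patient as receiving such care, and it mentions neither the baseline value nor site.

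Two other statements in Analyses bear on this. The general rule is that "Most of the secondary study outcomes are continuous and will be analyzed using a similar mixed modeling approach". Medication adherence (proportion of days covered, PDC), also a proportion within each patient, is compared both as a continuous measure by t-test and as a dichotomy with a stated cut-off of 0.80. Under Randomization, the design has an "allocation ratio of 1:1 and stratification by site".

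**The concern.** A proportion computed for each patient cannot go into a two-group chi-square test until every patient has been classed as yes or no. The article gives such a rule for PDC but not for guideline-concordant care. The definition and the test therefore describe different quantities, unless the second is meant class by class: among patients indicated for a given class, who receives it.

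On either reading the test uses only the 12-month value. The baseline value is collected, and what a patient is prescribed at the start probably predicts what that patient is prescribed a year later. Site was used to stratify the allocation and is also left out.

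At stake is the precision of a secondary result that readers will look to. The collaborative care team makes its recommendations against heart failure guidelines, so this between-arm comparison bears directly on whether the intervention changed treatment.

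**Working it through.** **1. The plan's own power figures.** The only power statements concern the KCCQ. With two-sided α = 0.05 (the article states 0.05 but not the sidedness) and n evaluable patients per arm:

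power = Φ( δ / (σ√(2/n)) − 1.96 )

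- Original: 600 × 0.70 / 2 = 210 per arm, δ = 5, σ = 18. 5 / (18 × 0.0976) = 2.846, so power = Φ(0.886) = 81.2%.
- Updated: 392 × 0.80 / 2 = 156.8 per arm, δ = 5, σ = 15. 5 / (15 × 0.1129) = 2.951, so power = Φ(0.991) = 83.9%.

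Both agree with the stated figure of more than 80%. No power is claimed for guideline-concordant care, so there is nothing to reproduce for this endpoint.

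**2. The two descriptions side by side.**

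| | Outcome measures | Analyses |
|---|---|---|
| Quantity | proportion within a patient | proportion of patients |
| Times | baseline and 12 months | 12 months |
| Link between the two | none given | none given |
| Baseline or site in the comparison | – | neither |

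The class-level reading removes the need for a cut-off, but it does not fit the per-patient definition and would give one comparison per class.

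**3. What dichotomising could cost (illustrative).** The article gives no distribution, number of criteria or number of indicated patients. Assume 156.8 evaluable per arm, a best case because the indicated subset can only be smaller, and a roughly normal score.

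- Information kept by a median split: 2/π = 0.637, about 64%.
- Effect giving the continuous score 80% power: (1.960 + 0.842) × √(2/156.8) = 0.316 SD.
- Power of chi-square on the same score, by the share of controls above the cut-off:

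| Controls above cut-off | 10% | 20% | 30% | 50% | 70% | 80% | 90% |
|---|---|---|---|---|---|---|---|
| Power | 42% | 53% | 58% | 60% | 53% | 45% | 32% |

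A real score over a few classes is coarse, so per-patient proportions were also simulated: beta-binomial, means 0.60 and 0.70, beta parameters summing to 4, 157 per arm, 4,000 runs.

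| Criteria per patient | t-test on proportion | All met | At least 80% met | At least 50% met |
|---|---|---|---|---|
| 3 | 76.9% | 65.2% | 65.2% | 61.7% |
| 5 | 87.6% | 67.3% | 75.2% | 70.5% |
| 8 | 92.8% | 64.8% | 78.3% | 70.7% |

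The loss varies with both the number of criteria and the rule. With a single indicated class the score is already 0 or 1, and dichotomising loses nothing.

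**4. What baseline adjustment could gain (illustrative).** In a linear model the variance falls by the factor 1 − r², where r is the assumed correlation between baseline and 12 months. The starting point is again 80% power at 0.316 SD.

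| r | 1 − r² | Variance cut | Power |
|---|---|---|---|
| 0.3 | 0.91 | 9% | 83.6% |
| 0.5 | 0.75 | 25% | 89.9% |
| 0.7 | 0.51 | 49% | 97.5% |

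These figures are for a linear score. They do not carry over directly to a logistic model of a yes/no outcome.

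**The case against.** The strongest reply is that chi-square fits a natural reading. The sentence on indications is about medication classes, and among patients indicated for a class, each either receives it or does not. No cut-off is then needed. This stands. It means that the text is ambiguous, not that the test is impossible.

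Second, the article refers to cited sources for criteria mapping, and it condenses a full protocol and analysis plan that are not shown. A classification rule and the date at which an indication is judged may well be set there. This also stands, so the absence of a rule in the article is not itself a fault.

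Third, an unadjusted 12-month comparison is valid in a randomized trial. That is agreed; the point here is efficiency.

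A reader might go further and infer three things that the document does not support:

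- **That a cut-off would be chosen after seeing the data.** Nothing in the article says or implies this.
- **That the analysis set is biased by arm, because closer review in the intervention arm uncovers new indications.** This holds only if indications arising in follow-up count, and the article does not say that they do.
- **That a fixed share of the information, such as 36%, is lost.** That share (1 − 0.637) rests on assumed normality and a median split.

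What remains is that two stated descriptions do not match as written, and that a stated test leaves collected data unused on either reading.

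**Conclusion.** The point holds in a limited form. The definition under Outcome measures and the test under Analyses disagree unless a class-by-class yes/no outcome is meant. On both readings the comparison forgoes the baseline value and the site strata, at a cost in precision and without bias. The size of that cost is unknown: it depends on the distribution of the score, the number of criteria per patient, the number of indicated patients and the correlation between baseline and 12 months, none of which the article gives. The power figures above show direction and plausible range only. The change is worth making because it replaces a stated test with a better-matched one at almost no cost.

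**What to change.** Make the main comparison the per-patient proportion at 12 months, adjusted for baseline proportion and site. Use either a linear model or a binomial model of criteria met out of criteria indicated; the binomial model should allow for correlation between criteria within a patient. Take each patient's indications from data at or before randomization, so that follow-up cannot affect who is analyzed or on which criteria.

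If a class-level yes/no outcome is what is meant, say so under Outcome measures and analyze each class by logistic regression adjusted for baseline receipt and site.

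The cost is a change of wording in the analysis plan. No new data are needed, since the baseline value is already scheduled and site is already known. The one small loss is that indications arising after randomization are left out of the main comparison.

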### Setting and population

The study is being conducted at the Denver, Palo Alto, Richmond, and Seattle VA Medical Centers and their affiliated community-based outpatient clinics. All patients with an assigned primary care provider and at least one primary care provider visit during the prior 12 months with a HF diagnosis code in the VA electronic health record were screened for eligibility to participate (see Figure 1 for study population flow).

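### Randomization is stratified by site, but the chi-square and t-tests named for hospitalization, mortality, guideline-concordant care and medication adherence ignore site: a minor, conditional loss of precision that costs almost nothing to remove

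*Protocol article*

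**What the plan says.** The Randomization section of the protocol article describes a computer-generated sequence "using a uniform fixed randomization design with an allocation ratio of 1:1 and stratification by site". It names no other stratification factor and gives no block size. There are four strata: "The study is being conducted at the Denver, Palo Alto, Richmond, and Seattle VA Medical Centers" (Setting and population).

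The Analyses section fixes the tests for several secondary outcomes:

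- All-cause hospitalization, mortality and guideline-concordant care at 12 months "will be compared between study arms using a Chi-Square test".
- PDC "will be compared as a continuous measure (t-test) and as the proportion of patients achieving a PDC > 0.80 (Chi-Square").

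No stratification or site term is attached to any of these. For the rest, the section says: "Most of the secondary study outcomes are continuous and will be analyzed using a similar mixed modeling approach". It lists no model terms for that approach or for the primary KCCQ model. PDC is continuous too, but the sentence about PDC is the more specific one, so I take the t-test as the stated analysis.

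Under Outcome measures, guideline-concordant care is limited to patients who have a guideline indication for the medication class.

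**The concern.** Stratifying by site, when allocation is restricted within site, removes site differences from the comparison of the arms. A plain chi-square or t-test does not take credit for this. It leaves between-site variance in its error term, so the standard error is larger than the real sampling variability of the estimate. The test then rejects less often than its nominal level under the null, and it loses power under the alternative.

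The outcomes concerned could well differ between facilities. What is at stake is precision on secondary outcomes, in a trial that closed at 392 patients after planning for 600 and that states no power for these tests.

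**Working it through.** **The plan's own figure.** The only power stated is for the KCCQ, with a 5-point difference and α = 0.05 (two-sided assumed). Power = Φ(δ / (σ√(2/n)) − 1.96), with n completers per arm.

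- 600 enrolled, 30% attrition: n = 600 × 0.70 / 2 = 210. With SD 18, 5 / (18√(2/210)) = 2.85, so power is 81.2%.
- 392 enrolled, 20% attrition: n = 392 × 0.80 / 2 = 156.8. With SD 15, 5 / (15√(2/156.8)) = 2.95, so power is 83.9%.

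Both agree with the article's claim of more than 80%. They concern the primary outcome and do not bear on this point.

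**Inputs for the secondary tests.** From the article: four sites, 1:1 allocation, 392 patients, α = 0.05. Assumed, because the article gives no site-level results: the site share of outcome variance ρ, or the site-specific event rates, and equal sites of 98 (4 × 98 = 392).

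**Continuous PDC, arms balanced within site.** The true variance is (1 − ρ) times the variance that the t-test uses. Hence:

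- standard error ratio r = 1/√(1 − ρ)
- real type I error = 2(1 − Φ(1.960 r))
- power of the plain test where the adjusted test has 80% = Φ(2.802 − 1.960 r)

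| Assumed ρ | SE too wide by | Real type I error | Power (adjusted test 80%) |
|---|---|---|---|
| 1% | 0.5% | 4.9% | 79.7% |
| 5% | 2.6% | 4.4% | 78.5% |
| 10% | 5.4% | 3.9% | 76.9% |
| 20% | 11.8% | 2.8% | 72.9% |

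**Binary outcomes, arms balanced within site.** Here r = √( p̄(1 − p̄) / mean of p_s(1 − p_s) ), where p_s is the rate at site s. The mean rate is assumed to be 40%. Type I errors come from 200,000 simulated trials per row, with 49 patients per arm at each site and no continuity correction.

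| Assumed site rates (%) | SE ratio | Plain chi-square | Site-stratified CMH |
|---|---|---|---|
| 40/40/40/40 | 1.000 | 0.050 | 0.049 |
| 35/38/42/45 | 1.003 | 0.049 | 0.050 |
| 30/35/45/50 | 1.013 | 0.046 | 0.050 |
| 20/35/45/60 | 1.047 | 0.040 | 0.050 |
| 10/30/50/70 | 1.124 | 0.027 | 0.050 |

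For an assumed 14-point difference, simulated power was 79.6% (plain) against 80.2% (stratified) at 30/35/45/50, and 80.3% against 83.2% at 20/35/45/60.

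The site share that each pattern implies is the variance of the site rates divided by 0.40 × 0.60 = 0.24. For 30/35/45/50 it is 0.00625 / 0.24 = 2.6%. For 20/35/45/60 it is 0.02125 / 0.24 = 8.9%. For 10/30/50/70 it is 0.05 / 0.24 = 20.8%.

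**No balance within site.** When each patient was assigned independently at 1:1 within site, the plain chi-square had a type I error of 0.050 to 0.051 in all five scenarios. It is not conservative in that case.

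**Subset outcomes.** If only a fraction f of each site's patients is analyzed, and f does not depend on arm, chance imbalance between sites returns in proportion to 1 − f. The true variance is then about (1 − fρ) times the variance used. With assumed f = 0.5 and ρ = 10%, r = 1/√0.95 = 1.026, an excess of 2.6% instead of 5.4%.

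**The case against.** **The loss is conditional.** It needs balance within site and outcomes that differ by site, and the article documents neither. This stands, and the conclusion carries both conditions. Stratification has little purpose unless allocation is restricted within the stratum, so balance is probably intended, but the article does not say so.

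**The large figures need extreme inputs.** This also stands. With a 40% event rate, an excess near 12% needs site rates of about 10% to 70%. Modest to sizeable site differences give roughly 0% to 5%.

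**The tests remain valid.** A conservative test does not inflate false positives. A reader might take the mismatch to make the secondary results untrustworthy; it does not.

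**The mixed models.** A reader might infer that the KCCQ model, and the models for the depression scales, also omit site. The article does not support this. It lists no terms at all for those models, and a condensed article may leave covariates to an analysis plan that is not shown.

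**The care team.** A reader might argue that site must be in the model because each site has its own nurse and collaborative care team. That team serves intervention patients, so its effect would appear as a difference between sites in the treatment effect. A site main effect does not address that, and it is not the mechanism calculated here.

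What remains is that the named tests ignore the only stratification factor, and that bringing it in has no material downside.

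**Conclusion.** The mismatch between design and analysis is plain from the article, but its consequence is small. It is confined to the outcomes with named tests: hospitalization, mortality, guideline-concordant care, PDC and PDC above 0.80.

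Given balance within site and a site share of variance of 1% to 10% (assumed), standard errors are about 0.5% to 5% too wide, the real type I error is about 4.9% to 3.9%, and power of 80% falls to between 79.7% and 76.9%. The excess is smaller for guideline-concordant care because of the restriction to patients with an indication. With equal site rates or unrestricted allocation within site, the tests keep their nominal level. Adjustment would still remove chance site imbalance and can recover precision where site predicts the outcome.

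Confidence is high that the stated tests do not match the stated design, and low for any particular size of loss, since no site-level data are given. This is a minor improvement; the primary conclusion is not affected.

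**What to change.** In the Analyses section, or in the analysis plan if it is still open:

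- Replace each chi-square test (hospitalization, mortality, guideline-concordant care, PDC above 0.80) with a Cochran-Mantel-Haenszel test stratified by site, or with logistic regression on arm and site. The Cochran-Mantel-Haenszel test is the easier choice if a site has few events.
- Replace the PDC t-test with a linear model containing arm and site.

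The models spend three degrees of freedom (four sites minus one) out of up to 392 patients. No new data are needed, and the change is a sentence or two. It should be fixed before outcomes are compared by arm, so that adjusting for site is not a choice made after seeing results.
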